In our survey of 1688 patients in 10 acute care hospitals, the prevalence of patients fulfilling MET criteria in the 24 h prior to data collection was 5.3% and on the day of observation was 3.3% [7]. Of the 55 patients who fulfilled the MET criteria, only 2 (3.6%) had a MET call activated within 24 h. Patients who fulfilled MET criteria at the time of vital sign acquisition were more likely to die in hospital (RR = 2.95; 95% confidence interval (CI) 1.22 to 7.15) or within 30 days (RR = 2.64; 95% CI 1.37 to 5.11). Our research has also shown the incidence of patients fulfilling MET calling criteria to be 14.4% during their hospital admission, and of those patients, only 2.9% received a MET call. Further, patients who fulfilled MET activation criteria had double the hospital length of stay [8]. Thus, timely and effective intervention is critical.

Although a growing body of international evidence demonstrates the benefit of early recognition and management of deteriorating patients, suboptimal management has serious consequences and represents a research-practice gap [12]. One recent study further highlighted this gap in a sample of 422 patients; escalation was indicated on 109 occasions, yet contrary to hospital policy, only 58 (53%) were escalated appropriately [6]. This failure to escalate and manage patients concurs with our previous research [7] and others internationally [3, 4, 13]. There is a need to understand the causes, mechanisms and strategies to overcome the problem using knowledge translation (KT) frameworks.

One widely researched and used KT framework is *the Promoting Action on Research Implementation in Health Services* (PARIHS) Framework [14–16], which views implementation as a dynamic and multi-faceted process. The proposition is that successful implementation is a function of the nature and type of evidence, the qualities of the context in which the evidence is being introduced, and the way the process is facilitated [15]. Although many strategies are thought to be effective in promoting individual and organisational change, the change agent role is believed to be a key ingredient for KT. Additionally, systematic reviews have found educational outreach of practice facilitation in health care have improved patient care [17, 18].

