### Secondary hypotheses

*Nursing practice outcomes*: Patients in wards receiving the FLIP will have increased documented VS (complete sets), repeated VS within 30 min of obtaining an abnormal VS, documented nursing scope of practice interventions in response to abnormal vital signs, increased activations for urgent clinical reviews and MET calls in patients fulfilling the criteria. *Clinical Outcomes*: Patients in wards receiving the FLIP will have fewer cardio-respiratory arrests, less unplanned intensive care unit (ICU) admissions, lower unexpected hospital mortality rates and reduced hospital length of stay (HLOS). *Health Economic Outcome*: The cost of implementing the FLIP will be offset by savings from shorter HLOS and reduced ICU admissions. FLIP will represent a cost-effective use of resources.

The study is designed to adhere to the Good Clinical Practice (GCP) Guidelines for national ethics standards and is consistent with the C-RCT CONSORT statement [19] and the CHEERS statement [20], ensuring it meets international ethical and scientific quality standards for reporting clinical trials that include an economic evaluation (see Fig. 1).

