### Sample size

From a medical record review in one of the sites, the rate of adherence to escalation policy after abnormal VS measurement was 53% [6]. Sample size calculations are based on a 50% rate of adherence to escalation as per hospital policy. To detect a 20% improvement in adherence rate in the intervention group immediately following and 6 months post-intervention, 270 documented abnormal VSs per time point per study arm are required. Our sample size has been inflated to allow for a design effect of 1.5, accounting for within-patient autocorrelation and within ward clustering effect. Type I error is set at a 1% significance level accounting for multiple comparisons and study power is set to 90%. For secondary outcomes, we have 80% power to detect an odds ratio of at least 1.8 in post-intervention comparisons for an improved adherence rate in the intervention compared to the control group. For all other secondary outcomes, power calculations have been based on combining immediately following intervention and 6 months post-intervention data. For the unplanned ICU admission rate, a minimum of 0.3% difference (1.2 vs 0.9%); for MET call rate a minimum of 2.3% absolute difference (3 vs 0.7%); and at least 1.6 day (IQR = 20) median absolute difference (12 vs 10.4) for hospital LOS is detectable at 80% power. Due to a low incidence of cardio-respiratory arrests and hospital mortality, a power analysis is based on combining mortality and code blue, resulting in 80% power to detect a minimum 2.3% absolute difference (3 vs 0.7%).

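### The 80% power stated for 3 vs 0.7% (MET calls and mortality/code blue) is not delivered by the planned size at the plan's own 1% alpha or with a clustering allowance, and the MET pair has no labelled arms or direction

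*Protocol article*

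**What the plan says.** All the power statements are in one paragraph, Sample size in the protocol article.

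- **Primary target:** "270 documented abnormal VSs per time point per study arm are required". The unit is the vital-sign record, not the patient. Alpha is set at 1% and power at 90%.
- **Clustering:** "Our sample size has been inflated to allow for a design effect of 1.5, accounting for within-patient autocorrelation and within ward clustering effect".
- **Other secondary outcomes:** "power calculations have been based on combining immediately following intervention and 6 months post-intervention data".
- **MET calls:** "for MET call rate a minimum of 2.3% absolute difference (3 vs 0.7"%), at 80% power.
- **Mortality and code blue combined:** "resulting in 80% power to detect a minimum 2.3% absolute difference (3 vs 0.7"%).
- **Neighbouring pairs in the MET sentence:** unplanned ICU admission 1.2 vs 0.9%, and median hospital stay 12 vs 10.4 days.

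None of these pairs says which figure is control and which is intervention. None comes with a number of patients, an alpha or a sidedness.

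Elsewhere in the article, Secondary hypotheses expects "increased activations for urgent clinical reviews and MET calls in patients fulfilling the criteria" on intervention wards. Secondary outcomes uses the same denominator, patients fulfilling the criteria. Background reports that 14.4% of patients met the criteria during admission and "of those patients, only 2.9% received a MET call"; a second survey there gives 2 of 55 (3.6%). Data analysis sets significance at p < 0.05.

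**The concern.** Two things do not fit together.

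1. **Size.** An 80% claim for 3 vs 0.7% should follow from the planned numbers, the stated alpha and the stated clustering allowance. Here it appears to need the clustering allowance set aside and an alpha other than the one in the same paragraph. It also appears to count vital-sign records as though they were patients, although death and arrest happen at most once or rarely per patient.
2. **Direction.** The neighbouring ICU and length-of-stay pairs put the higher value first, and both outcomes are hypothesised to fall under the intervention, so they read as control then intervention. In that order the MET pair describes a drop from 3% to 0.7%. The trial hopes to raise MET calls.

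What is at stake is how a null secondary result would be read. A non-significant difference in mortality/arrest or in MET calls would be set against a published 80% power that the planned size may not provide. For MET calls, the detectable change in the hypothesised direction is not given at all if 3% is the control rate.

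**Working it through.** **Inputs.** 270 records per arm per time point; two post-intervention time points pooled; design effect 1.5; alpha 1% (all Sample size). Alpha 5% (Data analysis). Allocation 1:1 (Randomisation). Rates 3% and 0.7%.

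**Formula.** Two proportions, pooled variance under the null, n per arm, two-sided:

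power = Φ[(d√n − z·s0)/s1], with d = |p1 − p2|, s0 = √(2p̄(1 − p̄)), s1 = √(p1(1 − p1) + p2(1 − p2)).

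For 3% vs 0.7%: d = 0.023, p̄ = 0.0185, s0 = 0.1906, s1 = 0.1899.

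**Step 1: reproduce the stated 80%.** n = 2 x 270 = 540, alpha 5% (z = 1.960):
(0.023 x √540 − 1.960 x 0.1906)/0.1899 = (0.5345 − 0.3735)/0.1899 = 0.848, power **80.2%**. Solving for n at 80% gives 538 per arm.

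**Step 2: use the paragraph's own alpha.** n = 540, alpha 1% (z = 2.576):
(0.5345 − 0.4909)/0.1899 = 0.230, power **59%**. At 1%, 80% power needs 801 per arm.

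**Step 3: allow for clustering.** Effective n = 540/design effect. The plan gives 1.5; 1.1 and 1.3 are my assumptions, because part of the 1.5 is for repeated measurements within a patient.

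| Design effect | Effective n per arm | Power, alpha 5% | Power, alpha 1% |
|---|---|---|---|
| 1.0 | 540 | 80% | 59% |
| 1.1 | 491 | 76% | 54% |
| 1.3 | 415 | 69% | 45% |
| 1.5 | 360 | 63% | 39% |

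With a design effect of 1.5 at alpha 5%, 80% power needs 538 x 1.5 = 807 per arm. One-sided testing does not recover the stated figure from the plan's inputs either: one-sided 5% gives 88% at 540 and 74% at 360; one-sided 1% gives 68% at 540.

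**Step 4: does the primary target carry the design effect?** 50% vs 70%, two-sided 1%, 90% power needs 176 per arm; 176 x 1.5 = 264, close to the 270 stated. So the inflation does seem to be in the primary number, and the 3 vs 0.7% figure then seems to use the inflated 270 at face value.

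**Step 5: do the pairs share one sample size?** ICU 1.2 vs 0.9% at 80% power, two-sided 5%, needs about 18,121 per arm; at 540 its power is about 7%. The ICU pair and the 3 vs 0.7% pair therefore cannot rest on the same number.

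**Step 6: the hypothesised direction.** If 3% is the control rate, a rise of 2.3 points to 5.3% has s0 = 0.2821 and s1 = 0.2816. At 540 and alpha 5%: (0.5345 − 1.960 x 0.2821)/0.2816 = −0.065, power **47%**; at an effective 360 it is 34%. The smallest rise from 3% with 80% power is to about 6.65% at 540 (3.65 points) and about 7.7% at 360 (4.7 points). If instead 0.7% is the control rate, 540 gives 3.0% as stated and 360 gives about 3.8%.

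**The case against.** The strongest reply is that 540 is reconstructed, not stated. The article gives no n or alpha for these lines, and other inputs also reach 80%. For example, 810 per arm at alpha 1% gives 80.6%, and 807 patients with a design effect of 1.5 gives 80% at 5%. Moreover, 270 is a minimum for the primary outcome, and the Assessments section reviews all inpatients on the study wards. Thirty-six ward facilitators at two per ward imply 18 intervention wards; at 18 or more beds each that is at least 324 beds, or 648 over two time points if full.

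Much of this stands. A reader might infer that the authors reached 80% only by treating clustered records as independent patients. The article does not prove that. But 810 = 3 x 270 would bring in baseline, against the stated pooling, and nothing in the article states 807 patients. The Sample/participants section follows up patients with abnormal vital signs, a subset of those in the beds, and MET calls are measured in patients fulfilling the criteria. The patient count is open in both directions.

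A reader might also take 63% as the corrected power, or 3 vs 0.3% as the corrected difference. That goes too far: the 1.5 partly covers within-patient repetition, which a once-per-patient outcome lacks, and the split is not given.

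On direction, the pairs may simply run from high to low. Per admitted patient, the Background gives 14.4% x 2.9% = 0.4%, nearer to 0.7% than to 3%. If 0.7% is control, the direction agrees with the hypothesis and two-sided power is unchanged. So a wrong direction is a strong inference from the neighbouring pairs and the 2.9% and 3.6% background rates, not a proof.

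Finally, the repeated pair may look like a copying slip. It need not be: the same n and the same 3% give the same 0.7%.

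It can also be said that the 1% alpha was meant for the primary comparison. Possibly, but the paragraph does not say so.

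**Conclusion.** The point holds as a defect in published power figures, not as an error in the design. With the planned 540 per arm, the stated 80% for 3 vs 0.7% matches two-sided 5% without clustering. Under the alpha or the clustering allowance that the same paragraph states, power lies between 39% and 76%, depending on which applies and how much of the 1.5 carries over to per-patient outcomes. The range assumes that 540 is the number analysed; the article gives no patient denominator, so a single replacement figure cannot be defended.

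The MET statement is also ambiguous in direction. On the more natural reading it describes a fall where an increase is hypothesised, and the same 2.3 points upward from 3% would have about 47% power even on the favourable assumptions (540, alpha 5%, no clustering).

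These are secondary outcomes and the primary sample size is untouched. The statements should nevertheless be corrected, because they will frame how null secondary results are read.

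**What to change.** - Label control and intervention for every pair in the Sample size section.
- Restate the MET figure as an increase from the control rate, on the denominator named under Secondary outcomes (patients fulfilling the criteria), with the expected number of such patients.
- Restate the mortality/code-blue power or detectable difference with the expected number of patients instead of vital-sign records.
- State one alpha and its sidedness for the secondary outcomes, and reconcile the 1% in Sample size with the p < 0.05 in Data analysis.
- Apply a ward-clustering allowance chosen for per-patient outcomes. If it is uncertain, show the range (for example design effects 1.1 to 1.5) in place of one value.
- Give the sample size behind the ICU pair, since it cannot be the one behind 3 vs 0.7%.

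The cost is text and less favourable stated figures. No change to wards, data collection or the primary analysis follows from this point.

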### Randomisation

Random 1:1 block randomisation of wards within hospitals to intervention or control groups will be undertaken. A central randomisation service independent of the study will be used with concealment until the intervention is assigned. Assessment days will be randomly selected.

### Control group

The control group ward staff will receive the standard implementation of CPGs. This will include information on the CPG, its availability online, as well as notification of the free online educational courses available to increase their knowledge and understanding about the identification and management of deteriorating patients. Information will be provided to each NM for dissemination to ward staff.

### Intervention group

The intervention group ward staff will receive the standard implementation of CPGs as described above plus the facilitation intervention for practice improvement (FLIP). FLIP comprises individuals in facilitator roles using facilitation methods and processes in a flexible way to tailor implementation strategies to the local ward context, according to identified barriers and enablers.

There will be two types of internal facilitator roles: hospital facilitators (HFLIP) and ward facilitators (WFLIP). A hospital facilitator will be appointed to cover four or five intervention wards in each of the four hospitals, acting as the overall facilitation lead and coordinator and mentor for the ward facilitators in each hospital. In each intervention ward, two ward facilitators will be appointed to support and enable ward nurses to implement the CPGs into practice (*N* = 36). Each HFLIP will be prepared and supported by an external expert in facilitation (GH). Each HFLIP will work with eight to ten WFLIPs. The facilitation intervention is underpinned by the PARIHS [14, 16] and i-PARIHS [21] frameworks.

Training and a toolkit of methods and techniques will be given to all FLIPs to promote the transfer of CPGs into daily practice. The intervention wards will receive 5 h per week support from the HFLIP for 6 months, reviewing barriers and enablers to implementing CPGs into practice prior to intervention commencement and in discussion with the WFLIPs. The HFLIP will provide face to face interactive education, including small group work, case presentations and role play, as well as review ward specific systems, processes, routines and audit practices in order to align systems of care to enable implementation of CPGs into daily practice. At ward level, the two WFLIPs will work with the HFLIP to audit practice, identify barriers, strategies and goals for improvement. They will provide cover for each other during leave and support ward staff during practice hours, receiving one day per fortnight of protected time for conducting audits, facilitation of ward nurses and meeting with the HFLIP to agree on strategies to improve adherence to guidelines.

### Recruitment and selection of facilitators

HFLIP positions will be advertised on the hospitals’ intranet and through a snowballing technique, to identify interested staff. Local staff will be interviewed and selected to build capacity within the participating organisations at a clinical leadership level. HFLIPs should have some prior experience (e.g. in practice development or an education role) so that they can support and mentor the WFLIPS and deal with the more challenging contextual barriers that may arise. Selection of all FLIPs will be based on the following characteristics: knowledge of and interest in NSQHC Standard 9; knowledge of colleagues, ward, and organisation; holds a clinical leadership role; and possesses good communication skills. Nurse managers will be asked to identify two WFLIPs for their wards based on the above criteria. All potential WFLIPs will be asked to consent to participation.

### Training and intervention fidelity

Research assistants (RAs) and facilitators will undergo onsite training to ensure consistency across all sites. Training will be tailored to the type of RA (outcome, process or economic assessor) or facilitation role (WFLIP or HFLIP) and be focused on consistency/fidelity. Standardised procedure manuals will be provided to all RAs and facilitators with specific detail on roles and responsibilities.

HFLIPs will receive training for 3 days from two experts in recognition and response to deterioration and advanced facilitation skills. HFLIPs will receive mentoring and ongoing support throughout the trial in a monthly teleconference with an external facilitator and Project Manager, as well as opportunities to teleconference at any time should questions or issues arise. One face to face HFLIP meeting and site visit will be conducted during the intervention. HFLIPs will receive contact details for other HFLIPs to encourage communication across sites, share learnings and troubleshoot barriers to facilitation. Ward FLIPs will receive training for a single day including knowledge on recognition and response to deterioration, beginner facilitation skills, and will receive mentoring and ongoing support during the trial. Support for WFLIPs will be provided by HFLIPs during the trial in the time allocated to each ward and via phone or email at other times. All interactions with WFLIPs will be captured by HFLIPs using electronic activity logs. Education modules, developed and used previously in research will be employed, including the following: using evidence in professional practice, implementing guidelines into practice, identifying and managing deteriorating patients, and facilitating and auditing. The intensity of the intervention will be monitored across sites. All HFLIP activities will be recorded on electronic activity and communication logs. HFLIPs will also audit ward practice 1 week each month for the duration of the intervention period. Audits will include half the occupied beds in each ward (every second bed). Audit data will be collected electronically and then formatted into feedback graphs and text. Text will contain a main message arising from the data. Feedback will be delivered to each WFLIP for discussion at ward meetings or individually to ward staff. WFLIPS will be taught the audit process to assist with their understanding of ward practices in relation to recognition and management of patient deterioration and for practice sustainability at the completion of the trial.

Research assistants performing data extraction from medical records will be given training on the electronic data collection tool and accompanying data dictionary. Inter-rater reliability testing will be established by independent double auditing across sites until Kappa >0.95 is achieved, with a minimum of 10 medical records audited per research assistant. In addition, a study monitoring audit will be conducted by the project manager on a random sample of 100 patient charts across four sites to ensure continued accuracy of data extraction by research assistants.

### Blinding

All RAs will be blinded to group allocation. Success of blinding will be assessed at study end using the James Blinding Index [22]. Although facilitators will not be blinded and nurses will be aware of the FLIP, ward nurses will be unaware of the comparator. Patients will be unaware of the intervention. MM, JW and the RAs will analyse the data, and all will be blinded to group allocation.

### Instruments

The electronic Case Report Form (eCRF) was adapted from our previous research [6, 7] to collect data relating to (1) documented vital signs (respiratory rate, heart rate, temperature, blood pressure, conscious state and oxygen saturation), CRC and MET activations; (2) patient outcomes, including unplanned ICU admissions, cardio-respiratory arrests, limitations of medical treatment orders, LOS and inpatient mortality; and (3) nursing interventions and referrals in response to abnormal vital signs and escalation as per hospital policy.

Electronic Activity and Communication Log (eACL) data will be collected at the time of activity and throughout the duration of the intervention. Data captured will include methods and techniques outlined in the Facilitator Manuals, enablers and barriers, and measures of impact.

### Assessments

#### Aims 1 and 2

Outcome data collection will occur across three time points: at baseline prior to implementation, immediately following completion of the intervention (6 months) and 6 months post-intervention (12 months). At each time point, the medical records of all inpatients admitted to study wards will be reviewed by a RA (blinded to group allocation) to determine if abnormal VS were present, and if so, the rates of escalation as per hospital policy, HLOS, unplanned ICU admissions and unexpected inpatient mortality. Data collection days will be randomly selected. RAs will be trained in data entry. Prior to RAs collecting data independently, inter-rater reliability will be evaluated by the project manager who is a registered nurse with specialist intensive care qualifications. Independent data extraction will be conducted until >95% agreement is obtained. The secure data entry system will not allow invalid values; data backup measures will be installed. Costs attributed to FLIP and training will be calculated.

#### Aim 3

Facilitators will complete electronic activity logs; ward communication and policy changes will be collected by RAs electronically. To capture the experience of FLIPs and key stakeholders regarding the intervention and CPG implementation, semi-structured individual and focus group interviews and field observations will be conducted at critical points in the project—before, during and after the intervention. Interviews will be audio-recorded and transcribed verbatim.

All assessments are outlined in Table 1.

**Table 1 Tab1:** Data collection

Aim	Variable/Measure	Instrument	Outcomes	Data collection point
1	Adherence to CPG	eCRF	CPG element compliance: completed VS documentation; repeated VS within 30 min; interventions within scope of practice; CRC and MET activations; escalation as per hospital policy.	Baseline^a^, 6 and 12 months^b^
2	Patient outcomes	eCRF; Hospital clinical databases	Unplanned ICU admissions, cardio-respiratory arrests, limitations of medical treatment orders, HLOS and inpatient mortality.	Baseline^a^, 6 and 12 months^b^
2	Hospital costs	CRF; Hospital clinical costing databases.	Unplanned ICU admissions, HLOS and inpatient mortality; total cost of hospital episode.	Hospital episode^b^
2	Intervention costs	CRF; Staffing salaries	FLIP cost; training frequency	Continuous
3	FLIP dose	eACL	Contact and content of contact.	Continuous
3	Enablers/barriers	eACL/ Ward Communication Books, RISKMAN incidents, Focus groups.	Issues arising; Critical incident analysis.	Continuous
3	Ward Impact	Ward Communication Books, policies and procedures, interviews, field observations.	Frequency and content.	Continuous
3	Facilitator Impact	Interviews with all FLIPS	Perceptions and content.	6 months^b^

^a^Prior to commencement of intervention (baseline)

^b^On completion of intervention (6 and 12 months post-baseline data collection)

